### Death

Patient survival will be calculated from the date of transplantation to the date of death for any cause.

### Graft loss

Graft survival will be calculated from the date of transplantation to the start date of chronic renal replacement therapy or listing for re-transplantation.

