### Randomization

Randomization will be performed using a predefined variable block randomization scheme, stratified by the participating centers and the age of the participant. Due to low expected patient numbers in the age groups of < 12 years and 12 to 18 years, patients in these age groups will be randomly stratified by age, but not by KTC. The randomization scheme will be generated and reviewed by the study biostatistician and quality assurance staff and locked by them after approval. The investigation sites will assign eligible patients through an interactive internet-based computer system (IWRS) once a patient has satisfied the requirements to be included in the study. The IWRS randomization tool is part of the eCRF (Secutrial^®^, interActive Systems, Berlin, Germany). After screening for eligibility and assignment of the individual PID, each patient can only be assigned once to one of the treatment arms. Using the web-based tool will make it impossible for the study personnel to predict the assignment. The sites will record the time of randomization. Treatment in the assigned group starts in the first year after the kidney transplantation and ends in month 12 after randomization.

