### Study endpoints

The primary endpoint will be measured via seven indicators: BAASIS Score (adherent) after 12 months, IPV of tacrolimus trough levels < 30% between months 6 and 12, number of unplanned hospitalizations in 12 months, number of unplanned hospitalizations > 10 nights in 12 months, normal 24h blood pressure profile at 12 months, no *de novo* DSA at 12 months, and eGFR ≥ 45ml/min at 12 months. Each indicator of the primary endpoint can be defined as achieved (=1) or not achieved (=0) for each patient. The primary endpoint is calculated by an unweighted sum of the achievement of the indicators (min = 0, max = 7). Secondary endpoints were graft failure within 12 months, better iBox prognosis at 12 months, increase in quality of life (self-report) over 12 months, increase in illness management (self-report) over 12 months, and incremental cost-effectiveness. In addition, acceptance of the patients and the telemedicine teams of the new telemedical approach will be measured.

*Adherence* will be determined by the BAASIS questionnaire (38) at month 12. Non-adherence is defined as “yes” to any of the questions. For patients without valid responses to the questionnaire, the response to the BAASIS questionnaire at month 9 will be imputed. Patients who did not respond to the questionnaire at months 9 and 12 will be considered non-adherent.

*Tacrolimus IPV* will be determined from tacrolimus trough levels at months 6, 7.5, 9, 10.5, and 12. To determine tacrolimus trough levels at months 7.5 and 10.5, patients will undergo a blood draw at home (either nephrologist or a general practitioner) or at a KTC according to the patient’s decision. If necessary, whole blood will be shipped by mail to the transplant center for central evaluation. For patients with tacrolimus levels of less than 3 (except for patients with graft loss or switch to another immunosuppressant), high tacrolimus IPV will be assumed.

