### Recommendation on the indication and timing of graft biopsies

The indication for kidney transplant biopsies is at the discretion of the investigator. Unless a biopsy is medically contraindicated, it is strongly recommended to perform a kidney biopsy under the following circumstances: any unexplained rise in creatinine ≥25% compared to baseline in absence of an obvious clinical cause for rising creatinine (e.g., ureteral obstruction, renal artery stenosis, dehydration, urosepsis, polyoma virus infection, or drug toxicity); in any case of clinical suspicion for rejection with/without an unexplained decrease in urinary output, fever, and graft tenderness; as soon as possible after starting treatment for suspected rejection; at development or worsening of proteinuria.

*Surveillance biopsies* are at the discretion of the investigator(s) and will be read locally. All data from protocol biopsies will be collected within the eCRF. Results of pre-transplant biopsies will be captured in the eCRF.

All biopsies should be read locally and classified according to the most recent Banff classification. In addition, biopsies may be read in a central laboratory at a later stage and documented within the eCRF. In the case of any BPAR, it is strongly recommended to perform local HLA antibody testing.

*Graft failure* is defined as the initiation of chronic dialysis for a period of more than 30 days, allograft nephrectomy, listing for re-transplantation, or death with a functioning graft following randomization. Graft survival will be calculated from the date of randomization to the date of graft failure.

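### Graft survival has two conflicting definitions, and the transplantation clock for graft and patient survival counts event-free time before randomization

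*Protocol article*

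**What the plan says.** Three places in the protocol article bear on this.

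- The Graft loss section: "Graft survival will be calculated from the date of transplantation to the start date of chronic renal replacement therapy or listing for re-transplantation".
- The graft failure definition, at the end of the section on indication and timing of graft biopsies. Failure is "initiation of chronic dialysis for a period of more than 30 days", or "allograft nephrectomy, listing for re-transplantation, or death with a functioning graft following randomization". It continues: "Graft survival will be calculated from the date of randomization to the date of graft failure".
- The Death section: "Patient survival will be calculated from the date of transplantation to the date of death for any cause".

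The Study endpoints section lists "Secondary endpoints were graft failure within 12 months" and gives no start date in that sentence. The Inclusion criteria admit patients transplanted within the previous 12 months who have stable function with eGFR above 30 ml/min. The Randomization section sets the trial's clock: "Treatment in the assigned group starts in the first year after the kidney transplantation and ends in month 12 after randomization".

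**The concern.** One term, graft survival, carries two calculation rules that differ in time origin and in events. The article does not say that they are separate measures, such as a death-censored and an all-cause version. Two analysts following the text could report different graft survival figures from the same data.

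The transplantation clock has a further fault. A patient who died or started chronic dialysis before entry cannot be in the trial. Each randomized patient therefore brings up to 12 months during which the event could not have been observed. If those months count as time at risk, the reported absolute survival is too high. The same holds for patient survival in the Death section. At stake are the absolute survival figures that readers would compare with other transplant cohorts, and the clarity of what graft survival means in the report.

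**Working it through.** **1. The two definitions side by side**

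| | Graft loss section | Graft failure definition |
|---|---|---|
| Start | Transplantation | Randomization |
| Dialysis | Start of chronic renal replacement therapy | Chronic dialysis lasting more than 30 days |
| Re-transplant listing | Yes | Yes |
| Nephrectomy | Not listed | Yes |
| Death with functioning graft | Not listed | Yes |

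Only re-transplant listing is the same in both. The start dates differ by 0 to 12 months per patient. Death-censoring alone would not explain the different start date, the missing nephrectomy or the missing 30-day rule.

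**2. Is the pre-randomization time really event-free?** Eligibility rules out prior death and, through stable eGFR above 30 ml/min, chronic dialysis. Earlier listing for re-transplantation is not named as an exclusion but is implausible with stable function at that level.

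**3. Size of the overstatement.** The article states no failure rate, so there is no figure of its own to reproduce. Assumptions: constant hazard h of 0.02, 0.04 or 0.06 per year; 12 months of follow-up from randomization; entry either fixed at 6 months after transplantation or uniform over 0–12 months; the same event list under both clocks; no delayed entry on the transplantation clock. Every event-free patient is then followed to at least 12 months after transplantation, so the 12-month failure read from each curve is:

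- from randomization: 1 − exp(−h)
- from transplantation, entry at 6 months: 1 − exp(−h/2)
- from transplantation, uniform entry: 1 − (1 − exp(−h))/h

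| h per year | From randomization | From transplantation, entry at 6 months | From transplantation, uniform entry |
|---|---|---|---|
| 0.02 | 1.98% | 1.00% | 0.99% |
| 0.04 | 3.92% | 1.98% | 1.97% |
| 0.06 | 5.82% | 2.96% | 2.94% |

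A simulation of 400,000 patients per setting agrees: 2.0%, 3.9% and 5.8–5.9% from randomization, against 1.0%, 2.0% and 2.9–3.0% from transplantation.

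**4. Person-time.** A mean of 0.5 years is added to a mean on-study time of (1 − exp(−h))/h years, which is 0.990, 0.980 and 0.971. The ratios are 1 + 0.5/0.990 = 1.51, 1 + 0.5/0.980 = 1.51 and 1 + 0.5/0.971 = 1.51 (simulated 1.50–1.52). Time at risk grows by about half with no added events.

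**5. Sensitivity to entry time.** With entry fixed at m months, the transplantation clock gives 1 − exp(−h(12 − m)/12). For h = 0.04, entry at 3 months gives 1 − exp(−0.03) = 2.96% and entry at 9 months gives 1 − exp(−0.01) = 1.00%, against 3.92% from randomization. The direction is fixed; the size depends on when patients actually entered.

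**The case against.** The secondary endpoint uses the term graft failure, and only one place in the article defines that term, with a randomization clock. The Graft loss section has its own heading, and the Baseline visit section lists graft loss and death among the items documented at visits. So the two rules could be a separately documented graft loss item without death and an all-cause secondary endpoint. Patient survival is not in the list of secondary endpoints, and delayed entry is a detail that an analysis plan may supply.

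Much of this stands. A reader might infer that the count for graft failure within 12 months is left open. The matching term, and visits and treatment timed from baseline or randomization, make the randomization-based definition the natural one.

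A reader might also infer that half of the on-study failures would be lost. That requires a cut-off at 12 months after transplantation, which the Graft loss section does not state. Without one, no event is discarded; each is given a longer survival time.

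Nor do the documents support a claim of bias between arms: eligibility applies to both arms before randomization, so pre-entry time is balanced in expectation.

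What the objection does not remove is that both rules are labelled graft survival and conflict, and that the transplantation clock as written overstates absolute survival. Delayed entry in an analysis plan would cure the second fault but not the first.

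**Conclusion.** The point holds as an inconsistency in a stated rule, of minor to moderate severity. Graft survival has two start dates and two event lists with no statement of how they relate. Followed as written, the transplantation clocks for graft and patient survival overstate absolute survival. Under an assumed constant hazard of 2–6% per year and mean entry at 6 months, the apparent 12-month failure is about 1–3% instead of about 2–6%. Those rates and entry times are assumptions, not trial figures. The calculation holds the event list constant, so it does not include the effect of counting or omitting death with a functioning graft.

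The conclusion goes no further. The arm comparison is not shown to be biased, and the primary endpoint is an unweighted sum of seven indicators, none of them a survival time.

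**What to change.** - Measure graft survival and patient survival from randomization to month 12 after randomization.
- Keep the four-event definition as the single definition of the secondary endpoint graft failure, and state that its 12 months run from randomization.
- If the Graft loss section is meant as a measure without death, give it its own name (for example death-censored graft loss), align its dialysis and nephrectomy terms with the graft failure definition, and start it at randomization.
- If any curve is shown from transplantation, let each patient enter the risk set at the randomization date (delayed entry).

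The cost is a few sentences and no obvious new data: the time of randomization is recorded, and the transplantation date is needed to check eligibility. The Trial status section expects the last patient out on 30 April 2026. The clarification should be dated and made before outcomes are analysed, so that the choice of definition cannot depend on results.

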### Acute allograft rejection

The diagnosis of BPAR (Banff grade ≥ 1A) will be based on histological grading using the current Banff criteria for renal allograft pathology [79]. A new episode of acute rejection will not be considered to have occurred until at least 30 days have elapsed since the last treatment for rejection. If less than 30 days have elapsed, additional therapy will be considered as reinitiation of treatment for an ongoing episode. Suspected rejections that are not proven by biopsy, but are treated with a course of anti-rejection therapy, will be defined as “treated rejections”.

### Recommendation on the indication and timing of graft biopsies

The indication for kidney transplant biopsies is at the discretion of the investigator. Unless a biopsy is medically contraindicated, it is strongly recommended to perform a kidney biopsy under the following circumstances: any unexplained rise in creatinine ≥25% compared to baseline in absence of an obvious clinical cause for rising creatinine (e.g., ureteral obstruction, renal artery stenosis, dehydration, urosepsis, polyoma virus infection, or drug toxicity); in any case of clinical suspicion for rejection with/without an unexplained decrease in urinary output, fever, and graft tenderness; as soon as possible after starting treatment for suspected rejection; at development or worsening of proteinuria.

*Surveillance biopsies* are at the discretion of the investigator(s) and will be read locally. All data from protocol biopsies will be collected within the eCRF. Results of pre-transplant biopsies will be captured in the eCRF.

All biopsies should be read locally and classified according to the most recent Banff classification. In addition, biopsies may be read in a central laboratory at a later stage and documented within the eCRF. In the case of any BPAR, it is strongly recommended to perform local HLA antibody testing.

*Graft failure* is defined as the initiation of chronic dialysis for a period of more than 30 days, allograft nephrectomy, listing for re-transplantation, or death with a functioning graft following randomization. Graft survival will be calculated from the date of randomization to the date of graft failure.

### Development of *de novo* donor- specific anti-HLA antibodies

Anti-HLA antibodies and dnDSAs will be analyzed locally throughout the trial at pre-specified visits, at the time of any suspected acute rejection, or according to local protocols. Any newly developed donor-specific HLA antibody with an MFI >1,000 will be classified as DSA. The development of dnDSAs at month 12 post-randomization is part of the primary combined endpoint. In addition, the incidence of anti-HLA antibodies at baseline and the incidence and time to development of *de novo* anti-HLA antibodies and dnDSAs will be calculated.

### Hypertension

Hypertension in adults is defined by the latest treatment guideline from the European Society of Cardiology (69). The interpretation of blood pressure levels depends on the patient’s age; risk constellation due to additional diseases, such as diabetes, chronic kidney disease, or coronary artery disease; and how the antihypertensive therapy has been accepted. Blood pressure that is too high starts with “high normal”, whereas all levels from grade 1 should lead to the immediate initiation of therapy. For definition, see above. The cutoff values for adults apply only to adolescents aged 16 years and older. Blood pressure of pediatric patients will be evaluated as follows: hypertension is defined in children as blood pressure (BP) above the 95th percentile for age, sex, and height. Grade 1 hypertension corresponds to BP values >95th percentile up to the 99th percentile + 5 mmHg, while Grade 2 hypertension is defined as BP >99th percentile + 5 mmHg. Only children above 3.5 years will be included and the percentiles from the KIGGS report will be used as the reference.

### Post-transplant diabetes mellitus

For the analysis of PTDM at month 12, only patients with no medical history of diabetes before transplantation will be included. Diabetes will be assessed through measurement of fasting plasma glucose and HbA1c and the need for any antidiabetic agents (oral or insulin) (70). PTDM is defined by the need for any antidiabetic agent (oral or insulin) and/or HbA1c > 48 mmol/mol (> 6.5%) at month 12 in a patient with no prior medical history of diabetes before transplantation. In addition, post-transplant hyperglycemia and newly developed PTDM within 12 months after randomization will be assessed. Post-transplant hyperglycemia is defined by a fasting plasma glucose level ≥ 126 mg/dL and/or afternoon capillary glucose level ≥200mg/dl with or without insulin requirement or the need for an oral antidiabetic agent in a patient with no prior medical history of diabetes. Newly developed PTDM is defined as PTDM in patients without diabetic medication at randomization. Finally, the incidence of HbA1c elevation will be determined by an increase a) > 42 mmol/mol (> 6.0%), b) > 48 mmol/mol (> 6.5%), and c) > 53 mmol/mol (> 7.0%) at month 12 after randomization.

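### Newly developed PTDM screens out only treated patients at randomization, so untreated patients already above the HbA1c limit can be counted as new cases

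*Protocol article*

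**What the plan says.** The relevant text is in the protocol article, section Post-transplant diabetes mellitus.

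- **Case definition.** "PTDM is defined by the need for any antidiabetic agent (oral or insulin) and/or HbA1c > 48 mmol/mol (> 6.5%) at month 12". There are two routes, and either one suffices.
- **Population for the month-12 analysis.** "only patients with no medical history of diabetes before transplantation will be included".
- **Incident outcome as announced.** "newly developed PTDM within 12 months after randomization will be assessed".
- **Incident outcome as defined.** "Newly developed PTDM is defined as PTDM in patients without diabetic medication at randomization".

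The Inclusion criteria admit patients whose transplantation took place up to 12 months earlier. The Exclusion criteria name no diabetes-specific condition. The Study endpoints section lists PTDM neither among the seven primary indicators nor among the secondary endpoints.

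**The concern.** The definition is asymmetric. A patient can become a case at month 12 through medication or through HbA1c alone, but only medication removes a patient who is already a case at randomization. The exclusion for earlier diabetes looks back to the time before transplantation, so it does not cover diabetes that arose between transplantation and randomization.

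A patient with untreated PTDM at randomization therefore stays in the at-risk set. If the patient still meets the definition at month 12, the event is reported as having developed after randomization. The reported incidence becomes a mixture of prevalent and incident cases, and a relative comparison of the arms is diluted by cases that the intervention could not have prevented.

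**Working it through.** The article states no PTDM rate, sample size or power, so there is no figure to reproduce. The check has a logical part, which needs no assumptions, and an illustrative part, which rests on assumed rates.

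**1. Which patients are classified differently?**

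Five yes/no facts determine the classification: diabetes before transplantation, medication at randomization, HbA1c > 48 mmol/mol at randomization, medication at month 12, and HbA1c > 48 mmol/mol at month 12. They give 2^5 = 32 combinations.

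- Rule as written: no earlier diabetes, no medication at randomization, and medication or raised HbA1c at month 12. Six combinations count as new: 2 baseline HbA1c states × 3 qualifying month-12 states.
- Rule that also requires HbA1c not above 48 mmol/mol at randomization: three combinations count as new.

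The three that change all have no earlier diabetes, no medication at randomization and raised HbA1c at randomization. At month 12 they show raised HbA1c, medication, or both. A patient who is back below the limit without treatment at month 12 is not counted under either rule.

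**2. Effect on the incidence (all rates assumed)**

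Among patients without earlier diabetes and without medication at randomization, let u be the share already above the HbA1c limit, q the probability that such a patient meets PTDM at month 12, and i the true 12-month incidence in the rest.

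- Rate as written = (1 − u)·i + u·q
- Rate with the restricted at-risk set = i
- Excess = u·(q − i), which is positive whenever q exceeds i
- Prevalent share of counted cases = u·q / [(1 − u)·i + u·q]

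With i = 5% and full persistence (q = 1):

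| u | Rate as written | Prevalent share of counted cases |
|---|---|---|
| 2% | 0.98 × 0.05 + 0.02 = 6.9% | 0.02 / 0.069 = 29% |
| 5% | 0.95 × 0.05 + 0.05 = 9.75% | 0.05 / 0.0975 = 51% |

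Over a wider assumed range (u from 1% to 10%, q of 50% or 90%), the rate as written runs from about 5.5% to 13.5% when i = 5%, and from 10.4% to 18.0% when i = 10%. The prevalent share of counted cases runs from about 5% to 67%.

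**3. Effect on the arm comparison (all rates assumed)**

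Take u and q equal in both arms, q = 90%, and true incidences of 10% (control) and 5% (intervention). The true risk ratio is 0.50 and the true risk difference is 5 percentage points.

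| u | Control | Intervention | Risk ratio | Risk difference (points) |
|---|---|---|---|---|
| 1% | 10.80% | 5.85% | 0.54 | 4.95 |
| 5% | 14.00% | 9.25% | 0.66 | 4.75 |
| 10% | 18.00% | 13.50% | 0.75 | 4.50 |

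The term u·q cancels from the difference, which is therefore (1 − u) times its true value. The risk ratio carries most of the distortion.

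**The case against.** The best defence is that the announcing sentence already limits the outcome to the 12 months after randomization. A patient above the limit at the start has not newly developed anything in that window, so the later sentence could be read as shorthand, with the exact at-risk set left to the full protocol or SAP. This softens the point but does not remove it. The defining sentence is complete and names its own criterion. Anyone programming from it would count these patients, so it is a stated rule that gives the wrong count, not an omitted detail.

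Other parts of the defence stand:

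- The article gives no untreated prevalence, persistence or incidence. The timing of enrolment shows that untreated prevalent cases are possible, not how many there are. A range of 5% to 67% for the prevalent share shows how little can be said about size.
- The general PTDM analysis at month 12 is unaffected.
- The article does not confirm that HbA1c was measured at baseline; the visit plan it refers to is not shown.

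Three stronger readings are tempting and not supported:

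- **That the trial's comparison is biased.** Randomization balances prevalent cases on average, so neither arm is favoured, and the primary endpoint does not use PTDM.
- **That any arm difference is substantially diluted.** This applies to the risk ratio. The risk difference shrinks only by the factor 1 − u.
- **That the three HbA1c-elevation incidences in the same section share the fault.** They are described as an increase above each limit, which can already mean crossing it from below. No error is shown there.

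**Conclusion.** The point holds as a defect in one outcome definition. Applied as written, the rule counts as newly developed any patient without earlier diabetes who is untreated and above the HbA1c limit at randomization and who meets PTDM at month 12. That conclusion follows from the text alone.

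The direction is an overstated incidence (provided persistence exceeds true incidence) and a risk ratio pulled toward 1. The absence of a systematic advantage for either arm assumes equal prevalence and persistence in both. The size cannot be determined from the article. The illustrative rise from 5% to about 7–10% depends on an assumed prevalent share of 2–5% and on full persistence, and would be smaller with less of either.

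Severity is low: this is an additional descriptive outcome with no hypothesis or power attached.

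**What to change.** Define newly developed PTDM as PTDM at month 12 in patients who have no diabetes before transplantation and who meet neither PTDM criterion at randomization, that is, no antidiabetic agent and HbA1c not above 48 mmol/mol. Use baseline HbA1c where it was recorded.

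If baseline HbA1c was not recorded, keep the present rule but label the outcome for what it is: PTDM at month 12 in patients untreated at randomization. Where it is missing for only some patients, state how they are handled.

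The cost is one clause in the analysis definition and a somewhat smaller denominator. No visit, measurement or treatment changes. The article reports that recruitment is finished, with the last patient out expected on 30 April 2026. The change therefore concerns the analysis only and should be settled before results by arm are seen. If baseline HbA1c was not collected, it cannot be added now, and relabelling is the only option.
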